## 9 Sample Size and Power Estimation

Power calculations depend on Moderna COVID-19 vaccine implementation, uptake, and the number of individuals meeting criteria for comparable vaccinated and unvaccinated cohorts.

We estimate that a total of 80,000 individuals will receive 2 doses of Moderna COVID-19 vaccine from December 2020 through March 2021, assuming 80% series completion (first interim analysis). We estimate an incidence of 30 COVID-19 diagnoses per 1,000 unvaccinated adult KPSC members during an average 4-month follow-up period (accounting for possible censoring). We expect to have >99.9% power to detect a VE of 70%, with various sample sizes in the unvaccinated group (Table 4), using a 2-sided test with  $\alpha=0.007$  (0.05 adjusted for 6 interim analyses and 1 final analysis). The calculation was performed using SAS software package (version 9.4) PROC POWER procedure.

Table 4. Power calculations for 1st interim analysis of Primary Objective 1 for various sample sizes and vaccine effectiveness estimates

| Sample Size Ratio
(Vaccinated vs
Unvaccinated) | Incidence rate in
unvaccinated group
(cases/1000 persons) | VE (%)
(reduction rate) | Power |
|------------------------------------------------------|-----------------------------------------------------------------|----------------------------|-------|
| 1 vs 0.5                                             | 30                                                              | 90                         | >.999 |
|                                                      | 30                                                              | 80                         | >.999 |
|                                                      | 30                                                              | 70                         | >.999 |
| 1 vs 1                                               | 30                                                              | 90                         | >.999 |
|                                                      | 30                                                              | 80                         | >.999 |
|                                                      | 30                                                              | 70                         | >.999 |
| 1 vs 5                                               | 30                                                              | 90                         | >.999 |
|                                                      | 30                                                              | 80                         | >.999 |
|                                                      | 30                                                              | 70                         | >.999 |

For the first interim analysis of Primary Objective 2, we estimate an incidence of 2 COVID-19 hospitalizations and 0.3 deaths per 1,000 unvaccinated adult KPSC members during an average 4-month follow-up period. We expect to have >99.9% power to detect a 70% VE against COVID-19 hospitalizations, with various sample sizes in the unvaccinated group (Table 5).

Table 5. Power calculations for 1st interim analysis of Primary Objective 2 for various sample sizes and vaccine effectiveness estimates

| Sample Size Ratio
(Vaccinated vs
Unvaccinated) | Incidence rate in
unvaccinated group
(cases/1000 persons) | VE (%)
(reduction rate) | Power |
|------------------------------------------------------|-----------------------------------------------------------------|----------------------------|-------|
| 1 vs 0.5                                             | 2                                                               | 90                         | >.999 |
|                                                      | 2                                                               | 80                         | >.999 |
|                                                      | 2                                                               | 70                         | >.999 |
| 1 vs 1                                               | 2                                                               | 90                         | >.999 |
|                                                      | 2                                                               | 80                         | >.999 |
|                                                      | 2                                                               | 70                         | >.999 |
| 1 vs 5                                               | 2                                                               | 90                         | >.999 |
|                                                      | 2                                                               | 80                         | >.999 |
|                                                      | 2                                                               | 70                         | >.999 |
| 1 vs 0.5                                             | 0.3                                                             | 90                         | 0.84  |
|                                                      | 0.3                                                             | 80                         | 0.69  |
|                                                      | 0.3                                                             | 70                         | 0.51  |
| 1 vs 1                                               | 0.3                                                             | 90                         | 0.93  |
|                                                      | 0.3                                                             | 80                         | 0.81  |
|                                                      | 0.3                                                             | 70                         | 0.62  |
| 1 vs 5                                               | 0.3                                                             | 90                         | 0.99  |
|                                                      | 0.3                                                             | 80                         | 0.97  |
|                                                      | 0.3                                                             | 70                         | 0.82  |

Based on the current Moderna COVID-19 vaccine implementation plan and anticipated uptake, we expect to accrue 500,000 to 1,000,000 individuals receiving 2 doses of Moderna COVID-19 vaccine for analyses of primary objectives by the end of 2021.

## 10 Statistical Analysis Plan for Vaccine Effectiveness Against SARS-CoV-2 Variants (Study Objectives 16-17)

As multiple SARS-CoV-2 variants of concern (VOCs) and variants of interest (VOIs) have been identified over the course of the pandemic, it is essential to identify the viral variant causing disease in this long-term effectiveness study. WGS of SARS-CoV-2 positive specimens from vaccinated and unvaccinated individuals will be performed to achieve the following secondary objectives:

16. Assess the VE of two doses of Moderna COVID-19 vaccine against SARS-CoV-2 variants (using both test-negative and cohort designs)
17. Assess the VE of one dose of Moderna COVID-19 vaccine against SARS-CoV-2 variants (test-negative design only)

To assess VE of 2 doses and 1 dose of Moderna COVID-19 vaccine against SARS-CoV-2 VOCs and VOIs (Secondary Objectives 16 and 17), we aim to use a test-negative design (TND). The TND includes all sequencing data and more easily facilitates both 2-dose and 1-dose VE analyses. In contrast, a cohort design includes all vaccinated individuals; however, the cohort analysis will only be conducted for the final analysis if the proportions of positive SARS-CoV-2 tests at KPSC and positive specimens sent for sequencing among COVID-19 cases (i.e., COVID-19 diagnosis outcome) are similar between vaccinated and unvaccinated groups; if the proportions are substantially different a cohort design will yield biased results. The threshold for testing individuals with symptoms suggestive of COVID-19 at KPSC does not differ by vaccination status. VOCs and VOIs will be selected for analyses based on prevalence in the KPSC population and scientific interest. Descriptive analyses will include the percentages of specimens from vaccinated and unvaccinated individuals sequenced with valid results, stratifying by cycle threshold (Ct) values, specimen type, and symptomatic/asymptomatic test types. We will also examine the proportions of vaccinated and unvaccinated individuals with each VOC and VOI overall, by specific characteristics (e.g., age, sex, race/ethnicity, immunocompromised status, other comorbidities, history of COVID-19), COVID-19 hospitalization/hospitalized death, and month of specimen collection.

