#### 4.3 SARS-CoV-2 Whole Genome Sequencing

KPSC began saving positive molecular SARS-CoV-2 test specimens in March 2021 to conduct whole genome sequencing (WGS). As part of this effort, all positive SARS-CoV-2 molecular test specimens from March 2021 to February 2022 will be sent to an external laboratory for sequencing and variant identification.

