### Statistical Analysis

Separate analyses will be conducted using the TND for 2-dose and 1-dose VE.

For each VOC or VOI, characteristics of test-positive cases and their matched test-negative controls will be described and compared. Specimens with unsuccessful sequencing may also be considered a test-positive case group for analysis. Continuous covariates such as age in years will be summarized by mean, standard deviation, median, quartiles, minimum, and maximum value, and compared using t-test or Wilcoxon rank-sum test, as appropriate; categorical covariates will be summarized by frequency and percentage and compared using chi-square test or Fisher's exact test, as appropriate. Absolute standardized difference will be calculated to assess the balance of covariates. Potential confounders will be determined based on bivariate analyses and scientific relevance. Given the small sample size and possible need to limit the number of covariates in an adjusted model, potential confounders will be determined by absolute standardized difference (ASD)  $> 0.1$  and  $p\text{-value} < 0.1$ , or scientific relevance.

Conditional logistic regression will be used to estimate the odds ratio (OR) and confidence intervals (CIs) of being vaccinated among cases vs controls, without and with adjustment for potential confounders determined from bivariate analyses. VE (%) will be calculated as  $(1 - \text{OR}) \times 100$ .

The TND analysis will be performed for both an interim analysis and a final analysis. For each interim analysis and final analysis, the test significance level will be adjusted using the Bonferroni correction,  $p = 0.025$  ( $= 0.05/2$  tests). As such, we will be calculating 97.5% CIs for each interim and final analysis. We will provide 95% CIs for each analysis as well. If sample

sizes allow, separate analyses using the same methods described above will be considered for VOCs and VOIs associated with severe COVID-19 disease (COVID-19 hospitalization).

For selected VOCs (e.g., Delta variant), if sample sizes allow, separate analyses will be conducted to assess the VE of Moderna COVID-19 vaccine against SARS-CoV-2 variants by time since most recent Moderna COVID-19 vaccination using the methods similar to those described above. Matching possibly will not be maintained in the subgroup analyses. Matching variables (age, sex, and race/ethnicity) and month of specimen collection will be kept in the adjusted model.

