## 10.2 Cohort design

The matched variant cohort will be developed in the same way as the matched cohort assembled for the primary analyses (Section 6.1 and Section 6.2, Study Objectives 1-2), using the same 2-dose Moderna COVID-19 vaccine exposure described in Section 7.1. Because Moderna COVID-19 vaccination began in December 2020 at KPSC, but archiving and WGS of SARS-CoV-2 positive specimens did not begin until March 2021, we will modify the matched cohort from the primary analysis to set index dates to begin no earlier than February 14, 2021 (14 days prior to March 2021). The cohort eligibility criteria will be applied based on the modified index date.

Baseline characteristics of the 2-dose Moderna COVID-19 vaccine cohort will be described and compared between the vaccinated and unvaccinated groups, as for the primary analyses above (Section 8.2). For each VOC or VOI, separately, the incidence of a specific VOC or VOI for the 2-dose vaccinated and unvaccinated individuals will be calculated by dividing the number of individuals with an incident COVID-19 diagnosis with a specific VOC or VOI by the total number of person-years. The person-years for an individual in the cohort will be the time from 14 days after the index date to the date of event of interest, death, disenrollment (allowing for a 31-day gap), end of follow-up (February 28, 2022), or receipt of a dose of any COVID-19 vaccine, whichever comes first. The event date is the date of the first incident COVID-19 diagnosis with a specific VOC or VOI after the index date. In addition, the follow-up time for individuals with an incident COVID-19 diagnosis for which the variant is unknown (i.e., sequencing unsuccessful or not sequenced) or different from the specific variant of interest will be censored on the date of the COVID-19 diagnosis. We will calculate incidence rates of specific VOCs and VOIs, unadjusted and adjusted HRs, and VEs, as described for the primary analyses above (Section 8.3)

If sample size allows, similar analyses will be conducted for VOCs and VOIs associated with COVID-19 hospitalization. Hospitalizations include hospitalized death, but there may be insufficient sample size to assess VE against COVID-19 hospitalized death by variant. Since the cohort analysis will only be conducted at the end of study (February 2022), no adjustment for multiple testing is needed.

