## 13 Limitations

This study has several potential limitations. Misclassification of the exposure is possible if COVID-19 vaccines were received outside of the KPSC system. However, external COVID-19 vaccination can be captured in the KPSC EHR data by manual entry and electronic updates from the California Immunization Registry (CAIR) (for which KPSC has a proactive mechanism in place for obtaining regular updates from CAIR). Misclassification of COVID-19 outcomes is also possible due to imperfect capture and sensitivity of SARS-CoV-2 molecular diagnostic tests. For variant VE analyses (Secondary Objectives 16-17), sequencing may be unsuccessful if viral loads are low, which may be more common among vaccinated vs. unvaccinated individuals. However, samples with unsuccessful sequencing may also be considered a test-positive case group for analysis. For patients with COVID-19 symptoms, sensitivity of molecular diagnostic tests is generally high (>90%). Efforts are made to ask patients about positive tests conducted outside of KPSC and to document in the EHR with internal diagnosis codes. In addition, we will be unable to capture some potential confounders, such as occupational risk exposures, behavioral factors (e.g., masking, distancing, handwashing), and residential factors (e.g., congregate settings) that impact an individual's risk for COVID-19. Thus, despite all efforts to ensure comparability, there may be some unmeasured differences between vaccinated and unvaccinated cohorts. Some secondary analyses may be underpowered; their meaningfulness will depend on uptake of Moderna COVID-19 vaccine in these patient populations.

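### The check that permits the variant cohort analysis stops at specimens sent for sequencing, so neither variant design guards against sequencing failing more often in the vaccinated, which would overstate variant-specific VE

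*Protocol*

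**What the plan says.** Section 10 of the protocol makes the cohort variant analysis conditional. It is run, at the final analysis only, if the "proportions of positive SARS-CoV-2 tests at KPSC and positive specimens sent for sequencing among COVID-19 cases" are similar by vaccination group. The reason given is that "if the proportions are substantially different a cohort design will yield biased results".

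Section 4.3 states that "all positive SARS-CoV-2 molecular test specimens from March 2021 to February 2022 will be sent to an external laboratory".

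Section 13 names a later step at which cases can be lost: "sequencing may be unsuccessful if viral loads are low, which may be more common among vaccinated vs. unvaccinated individuals".

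The two designs treat failed specimens as follows:
- **Cohort (Section 10.2).** Follow-up of a case "for which the variant is unknown (i.e., sequencing unsuccessful or not sequenced) or different from the specific variant of interest will be censored" at diagnosis. Such a case is not an event for any named variant.
- **Test-negative design (TND, Section 10.1).** The outcome list has a category for unknown lineage, and the analysis text adds: "Specimens with unsuccessful sequencing may also be considered a test-positive case group for analysis".

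Section 10 also plans a table of sequencing success: "Descriptive analyses will include the percentages of specimens from vaccinated and unvaccinated individuals sequenced with valid results", broken down by cycle threshold (Ct), specimen type and symptomatic or asymptomatic test type. No decision or correction is tied to that table.

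**The concern.** A COVID-19 case becomes a variant event only after three steps: a positive test at KPSC, a specimen sent, and a valid sequence. The check in Section 10 compares the first two steps between the groups. The third is the one that Section 13 singles out as possibly differing by vaccination status, and the check does not look at it.

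In the TND there is no check at all. TND controls need no sequencing, so the loss on the case side has nothing to offset it. A failed positive specimen cannot become a control either, because controls must have no positive test from 1 March 2021.

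If sequencing fails more often in vaccinated cases, those cases are removed preferentially from every named variant and VE looks better than it is. The distortion in VE is largest where true VE is lowest. If success also changes with time since vaccination, the planned Delta analysis by time since vaccination (Section 10.1) would be affected as well.

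**Working it through.** **The plan's own figures (Section 10.3).** Both reproduce.
- TND: 1:5 matching, 60% of controls vaccinated, VE 0.8 (OR 0.2), two-sided alpha 0.025, power 80%. Exposure in cases is 0.2 × 0.6 / (0.4 + 0.2 × 0.6) = 0.231. The two-proportion formula with five controls per case gives 20 cases, as stated. A matched case-control formula gives 19.3 at within-set correlation 0 and 20.2 at 0.1.
- Cohort: 1:1, VE 0.8, two-sided alpha 0.05 (inferred, since Section 10.2 makes no multiplicity adjustment). Freedman's formula gives (1.96 + 0.84)² × (1.2/0.8)² = 17.7, so 18 events in total and 18/1.2 = 15 in the unvaccinated, as stated.

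These numbers are not in dispute. They count cases with a known lineage.

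**What the check can see.** Its denominator is all COVID-19 diagnosis outcomes. Section 7.2 counts a diagnosis code alone as an outcome. Section 4.2 shows that in 2020 such cases were 295,395 − 238,643 = 56,752, or 19% of diagnosed members. The text says these include positive tests from outside KPSC and clinical diagnoses. The sent proportion can therefore differ by vaccination status, and the check tests something real. Among KPSC positives, however, Section 4.3 sends every specimen, so within that group the sent proportion is near 100% in both arms whatever happens in the laboratory.

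**Size of the bias.** Let s_v and s_u be the proportions of sent specimens that sequence successfully in vaccinated and unvaccinated cases of a given variant. Only successes count, so

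observed ratio = true ratio × (s_v / s_u), and VE_obs = 1 − (1 − VE) × (s_v / s_u).

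This applies to the HR in the cohort and to the OR in the TND. The documents give no value for s_v or s_u, so the rows below are assumptions.

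| Success, vaccinated v unvaccinated | s_v/s_u | True VE 80% reads | True VE 70% reads | True VE 50% reads |
|---|---|---|---|---|
| 90% v 90% | 1.000 | 80.0% | 70.0% | 50.0% |
| 80% v 90% | 0.889 | 82.2% | 73.3% | 55.6% |
| 70% v 85% | 0.824 | 83.5% | 75.3% | 58.8% |
| 60% v 85% | 0.706 | 85.9% | 78.8% | 64.7% |

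Example: 1 − 0.50 × (0.60/0.85) = 1 − 0.353 = 64.7%.

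The cohort version, with failed specimens censored at diagnosis, was checked by simulation at success of 70% v 90%. True VE of 80% and 50% came out at 84.7% and 61.1%, against 84.4% and 61.1% from the formula. In every row the sent proportion can be 100% in both groups.

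**The case against.** The strongest reply is that the protocol already deals with this. It discloses the limitation, tabulates valid-result percentages by vaccination status, lists unknown lineage as an outcome and allows failed specimens to be analysed as a case group. A reader of the results could see s_v and s_u. All of that is true. What remains is that the table triggers nothing, and a separate group of failed specimens does not change the VE of any named variant. Nor can this be left to a separate analysis plan: Section 10 is titled as one, and it fixes both the check and the censoring rule.

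Some stronger readings are tempting, and the documents do not support them:
- A reader might infer that the check will pass whatever the data, because all positives are sent. Its denominator includes code-only cases, so it can fail. It is blind only to sequencing failure.
- A reader might infer that the protocol expects differential failure, so that variant VE will be inflated. Section 13 says only that failure may be more common in the vaccinated. The bias is conditional on that difference.
- A reader might treat the check as the safeguard for all variant results. It governs the cohort analysis alone. Changing it leaves the TND untouched.

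Two further points stand. At the VE of 80% used for planning, the distortion is 2 to 6 percentage points. At the minimum of 15 unvaccinated cases (about 3 vaccinated), the standard error of log HR is √(1/15 + 1/3) = 0.63, so the 95% interval for VE is about 31% to 94%, far wider than the bias. The bias matters mainly for common variants.

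**Conclusion.** The point holds in conditional form. The check on the cohort analysis omits sequencing success, and the TND has no check. Neither design returns failed specimens to a named variant. If success is lower in the vaccinated, VE is overstated by (1 − VE) × (1 − s_v/s_u). Over the assumed range that is 2 to 6 points at a true VE of 80%, 3 to 9 at 70% and 6 to 15 at 50%. The direction follows from the possibility stated in Section 13. The size rests on assumed success rates, because the documents give none.

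Severity is moderate. Secondary Objectives 16 and 17, and the two variant manuscripts in Table 6, are affected. The primary objectives do not use lineage and are not.

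**What to change.** 1. **Cohort check.** Add to the existing criteria the proportion of COVID-19 cases with a lineage successfully assigned, by vaccination status. State what counts as similar, and whether a failed check cancels the analysis or triggers a correction.

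2. **Both designs.** For variants with enough cases, prespecify a sensitivity analysis that corrects for sequencing failure and report it beside the uncorrected VE. It can use inverse-probability-of-sequencing weights or imputation of lineage, based on vaccination status, Ct (within assay, since Section 4.2 describes several platforms), specimen type, test type and month. At minimum, rescale with the observed success proportions: corrected VE = 1 − observed ratio × (s_u / s_v). For example, an observed ratio of 0.412 with success 70% v 85% gives 1 − 0.412 × (0.85/0.70) = 50%. Rescaling assumes that, within vaccination group, success does not depend on lineage.

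The cost is protocol wording and one extra model. Ct, specimen type, test type and valid-result status are already to be tabulated, so no new data are needed for sequenced or failed KPSC specimens. Intervals will be wider. With 15 to 20 cases per variant the correction will be unstable, which is why it is proposed as a sensitivity analysis. Weighting cannot recover specimens whose viral load is too low ever to sequence, and code-only cases have no Ct or specimen type.
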